## Methods

To evaluate the impact of the SCRT, we will use a QUANT-QUAL mixed methods implementation science approach [14, 15]. First, we will use quantitative methods to examine if there are changes in utilization of mental health, substance use, and housing services as well as jail entry following implementation of the SCRT among PEH who present in behavioral health crisis to acute care settings within San Francisco’s public health system. Second, we will evaluate the ability of the SCRT to enhance equity by stratifying our analysis by ethnoracial groups to examine pre-implementation disparities as well as post-implementation worsening, perpetuation, or resolution of baseline disparities. We will use our quantitative analysis to set the sampling frame for qualitative semi-structured interviews, which will be conducted with the SCRT service recipients to understand the facilitators and barriers to achieving their goals. Finally, we will consider the quantitative and qualitative results in combination to help interpret both sets of findings.

Study procedures were approved by the University of California, San Francisco, Committee on Human Subjects Research (Protocol #20–32693). The Committee waived consent for review of healthcare, housing, and jail records, and approved verbal informed consent procedures for telephonic and in-person interview participants.

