### Program

The Behavioral Health Services division of the San Francisco Department of Public Health (SFDPH) has an extensive infrastructure for mental health and substance use disorder services, yet one important gap has remained: real-time response for people in behavioral health crisis in the streets. In 2019, San Francisco’s 9-1-1 call data indicates that approximately 50,000 behavioral health related calls were received, most of which were responded to by a law enforcement unit. Because most calls were not related to criminal events, and instead to mental health and social needs experienced by PEH, San Francisco behavioral health and governmental leaders worked with community stakeholders to create the SCRT to respond as an alternative able to be more responsive to behavioral health crises that happen on the street [16].

The SCRT was designed based on previous co-responder models [17, 18]. To meet the goal of diverting calls that would typically go to the San Francisco Police Department, this trauma-informed specialty behavioral health team is dispatched solely by 9-1-1 operators. The SCRT utilizes a co-responder model comprised of a behavioral health clinician, a paramedic from the San Francisco Fire Department and a peer specialist. Each team member plays a role in providing care including immediate stabilization of urgent medical need (paramedic), de-escalation of the crisis (behavioral health clinician) and person-centered peer support (peer specialist). The team triages clients to the appropriate level of care, be it through resolution of the crisis in the field, linkage to outpatient mental health and substance use services, or transport to an acute treatment setting. The SCRT was first piloted in San Francisco’s highest demand neighborhoods in December 2020 and then was incrementally expanded to be citywide by June 2021 (Fig 1).

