#### Study population

The SCRT aims to provide specialty mental health response and enhanced resources to adults in San Francisco who experience crises related to mental health and/or substance use disorders and are experiencing homelessness. Therefore, the study population will be defined based on age greater than 18 years, meeting criteria for homelessness in the 12 months prior to or 3 months following the crisis episode, and receipt of crisis care from any of San Francisco’s “front door” programs for people in an acute behavioral health crisis. These settings include two mobile crisis programs (Comprehensive Crisis Services and the SCRT), a crisis stabilization unit (DORE Urgent Care Clinic), and emergency psychiatric services (Zuckerberg San Francisco General Hospital’s Psychiatric Emergency Services [PES] and Emergency Department visits with a primary behavioral health diagnosis) (Fig 2). The population of housed adults utilizing acute behavioral health services will be utilized as a control group in the ITS sensitivity analyses.

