#### Index crisis episode

Conducting an ITS that includes a time-dependent outcome—in this case a routine care episode, acute care episode, housing assessment, or jail entry within 30 days following a crisis episode—requires defining an index crisis episode to start the clock for the outcome time interval. Furthermore, given that there may be multiple index episodes per unique individual, the index crisis episode needs to be defined per ITS interval, which, based on our preliminary power analysis, will be divided as one calendar month per interval. The index crisis episode will therefore be defined as the first instance in a given month that an individual has a crisis episode, with the 30-day post-crisis outcome period trailing the end date of the index episode.

We also need to account for the fact that a single crisis episode may result in multiple contacts with different settings in the acute behavioral health care system. To account for this variability, we will use our clinical knowledge of common care pathways as the basis for a crisis system map (Fig 2) that defines different sequences of care as either a step-up in service intensity (e.g., mobile crisis followed by crisis stabilization or ED), a step-down in service intensity (e.g., PES followed by crisis stabilization), or a distinct crisis episode that mostly likely signifies reutilization (e.g., PES followed by mobile crisis, or two consecutive mobile crisis episodes). We will then combine sequences with a step up or down in service intensity that occur within two or fewer days between the end of the first and start of the second clinical setting, so as not to miscount these care transitions as reutilization. This approach also allows us to create a variable describing these crisis system trajectories, thus allowing us to identify potential differences between index crisis episodes based on crisis system entry point and end point. All crisis services utilized three or more days after the index crisis episode end date will be considered separate from the index crisis episode.

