#### Interrupted time series analysis

The ITS analysis will examine three periods: 1) Pre-SCRT baseline (November 2019 to November 2020), 2) SCRT partial implementation (December 2020 to July 2021), and 3) SCRT full implementation (August 2021 to August 2022). Each of the outcome measures will be computed as a monthly proportion, with the numerator equaling the number of individuals meeting criteria for each outcome and the denominator equaling the total target population in a given month. Using month-long time intervals would yield between 8 and 12 data points per time period, though the final interval length may change depending on the trade-offs between length of observation and statistical power.

Generalized estimating equations (GEE) will be used, with robust standard errors to account for within-person correlation [27], to analyze the trends in outcomes pre-implementation, during partial implementation, and after the implementation of SCRT. Models will include a variable for time (month) after the beginning of our observation period, a variable for time each time period subsequent to baseline, and the interaction between these variables to assess change in the trajectory of each outcome. Models will be adjusted by the covariates described above and interaction terms constructed to understand the relative effects of covariates and the ITS variables.

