This analysis will use several design and analysis strategies to account for potential threats to internal validity. First, the study design using two nonequivalent groups with staggered implementation (crisis episodes with zip codes corresponding to neighborhoods that did or did not have the SCRT active during the partial implementation phase prior to citywide expansion) will allow for a between-site comparison of the pilot catchment area relative to the non-pilot areas (Fig 1). Additional sub-analyses will examine within-site differences for the pilot neighborhoods across the three time periods, and, separately, within-site differences for the non-pilot neighborhoods. Second, a non-equivalent non-treatment control group (non-homeless adults accessing crisis services) will be compared to the target population (homeless adults accessing crisis services) using a difference of differences approach to account for secular variations in mental health and substance use service utilization. Third, a series of non-equivalent dependent outcome variables that are not expected to be impacted by the implementation of the SCRT (e.g., non-crisis initiation of outpatient mental health services) will be evaluated across the same time periods with a similar goal of accounting for secular variations in mental health service utilization. Additional issues such as autocorrelation of repeated measures on individuals will be corrected for in the final analyses.

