### Mixed methods analysis

Once both the ITS and qualitative analyses have been completed, the results of each will be examined in conjunction with the other to assist with interpretation of the overall study findings. For example, measuring quantitative service utilization outcomes among interview participants can help inform how we interpret their reports of how SCRT impacted their lives. If the equity analyses produce concerning signals for disparities in care, we could incorporate this information into how we analyze qualitative findings about discrimination. Another example would be if we find a lack of significant change in the ITS analysis of post-crisis routine care utilization after implementation of SCRT, in which case our interpretation may be informed by qualitative descriptions of barriers to accessing routine care. These kinds of mixed methods approaches allow us to leverage the nuanced details of qualitative research and the more representative findings in population-level quantitative research to arrive at a stronger set of interpretations and conclusions.

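### The time series estimates a system-wide change among all homeless crisis users, but the plan carries it toward SCRT's effect on its clients without regard to how many were reached

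*Protocol article*

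**What the plan says.** The Interrupted time series analysis section computes each of the four outcomes as a monthly proportion, with "the denominator equaling the total target population in a given month". The Study population section admits people on "receipt of crisis care from any of San Francisco’s “front door” programs for people in an acute behavioral health crisis" and then names the doors: "These settings include two mobile crisis programs (Comprehensive Crisis Services and the SCRT), a crisis stabilization unit", followed by psychiatric emergency services and emergency department visits with a behavioral health diagnosis. SCRT is therefore one door of five. The Program section says that "this trauma-informed specialty behavioral health team is dispatched solely by 9-1-1 operators", and the follow-up service is offered after an SCRT encounter. A person who enters by another door, with no SCRT contact, does not receive the intervention.

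The Methods section puts the question at system level: whether use of services and jail entry change after SCRT starts, "among PEH who present in behavioral health crisis to acute care settings".

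Two later sections go further. The Mixed methods analysis section takes the case in which routine care shows no significant change and says that "our interpretation may be informed by qualitative descriptions of barriers to accessing routine care". The Discussion describes the study as explaining how effective SCRT is at keeping its clients out of further crisis services and jail and at linking them to care.

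The Index crisis episode section creates a variable for the path through the crisis system, by entry and end point. Neither the Covariates section nor the ITS section names it. The Limitations section does not mention reach.

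**The concern.** A change averaged over all homeless crisis users and a change among people SCRT reached are different quantities. The ITS estimates the first, and parts of the plan talk about the second. The number that connects them, the share of index episodes with an SCRT contact, enters neither the estimate nor its planned interpretation.

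At stake is the meaning of a non-significant result. Low reach alone can produce one, whether or not routine care is hard to access. A reader who goes straight to barriers has skipped an explanation that the study's own data could check. A significant result has a similar difficulty: SCRT is a new way into the counted population, so part of a change may come from who is counted.

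**Working it through.** **Plan's own figure.** There is none to reproduce. The article gives no SCRT share, baseline rate, effect size, sample size or power. All numerical inputs below are assumptions, chosen to show the range.

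**Inputs**
- s: SCRT share of the post-launch denominator. Assumed 10% to 50%.
- d: change in the outcome among those reached. Assumed +10 percentage points.
- p0: outcome rate before SCRT. Assumed 30%.
- f: fraction of those reached who would not have been in the denominator before SCRT existed. Assumed 0, 50% or 100%. The Program section makes f above 0 plausible: most 9-1-1 behavioral health calls had been answered by police, and such people counted before launch only if they also reached another listed door.
- q: outcome rate that the newly counted people would have without SCRT. Assumed 15% or 45%.

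**Formula.** With no spillover to people not reached, the post-launch rate is (1 - s)p0 + s[(1 - f)p0 + fq] + sd. Subtracting p0 gives

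observed change = s × d + s × f × (q - p0).

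**Stable case mix (f = 0).** The second term vanishes and the change is s × d:
- s = 10%: 0.10 × 10 = 1.0 point
- s = 20%: 2.0 points
- s = 30%: 3.0 points
- s = 50%: 5.0 points

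In this setting, an interval rules out a 10-point effect in clients only if it excludes 1 point at a 10% share, or 5 points at a 50% share.

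**SCRT brings in new people (f above 0)**

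| s | f | q | Change with d = 10 | Change with d = 0 |
|---|---|---|---|---|
| 30% | 50% | 15% | 3.0 - 2.25 = +0.75 | -2.25 |
| 30% | 50% | 45% | 3.0 + 2.25 = +5.25 | +2.25 |
| 30% | 100% | 15% | 3.0 - 4.5 = -1.5 | -4.5 |
| 30% | 100% | 45% | 3.0 + 4.5 = +7.5 | +4.5 |
| 50% | 100% | 45% | 5.0 + 7.5 = +12.5 | +7.5 |

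The observed change can be smaller than the effect in clients, opposite in sign, or larger (12.5 against 10).

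**Dividing by the share.** At s = 30% and no true effect, the two extreme cases give -4.5 / 0.30 = -15 and +4.5 / 0.30 = +15 points. Division therefore does not recover a per-contact effect unless case mix is stable and there is no spillover.

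**Index rule.** Only a person's first crisis episode in a month is the index. A later, separate SCRT contact in that month is not, so the share of index episodes can understate reach.

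**The case against.** The strongest reply is that the denominator is right. The Methods section asks a population question, and the Mixed methods analysis section describes the quantitative findings as population-level. SCRT recipients have no counterpart before launch, and restricting to them would select on receipt of treatment. This stands in full: a reader might infer that the ITS uses the wrong population, and the documents do not support that.

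Three other stronger readings also fail.
- A reader might infer that the plan will call SCRT a failure if the result is null. The text offers one example and says only that interpretation may draw on barriers. It sets no decision rule, and the Limitations section concedes that the design may not be definitive.
- A reader might infer that the ITS cannot detect a realistic effect. The article's one statement on power concerns interval length: "based on our preliminary power analysis, will be divided as one calendar month per interval". It does not say what effect was assumed, so no power figure can be derived.
- A reader might infer that the effect is always shrunk by the untreated share. The table shows that this needs stable case mix and no spillover.

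The plan also has partial safeguards. The comparisons of pilot with non-pilot areas and of homeless with housed adults address secular change. Covariate adjustment, including diagnosis and prior-year service use, would absorb some measured change in case mix; the figures above are unadjusted. But pilot-area denominators still mix SCRT and other episodes, and the 9-1-1 dispatch data that might show who was diverted from police will not be available.

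Finally, reporting a share could be left to a fuller document. That is fair as far as omission goes. The point here is a mismatch within the article, between the quantity estimated and the conclusions it describes.

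**Conclusion.** The point holds as a mismatch between estimand and interpretation. The ITS gives a legitimate system-wide change. It does not by itself show SCRT's effect on its clients, and a non-significant result cannot be tied to care barriers without regard to reach.

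The size is unknown because the article gives no share. Under an assumed 10-point effect in those reached, stable case mix and no spillover, the system-wide change is 1 to 5 points for shares of 10% to 50%. If SCRT also changes who is counted, the series can move either way without any effect: by up to 4.5 points at a 30% share under the assumed rates. The mismatch itself rests on the text and not on these assumptions. It is worth correcting because it bears on what the study may conclude, and the correction is cheap.

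**What to change.** In the Interrupted time series analysis section:
- State that each coefficient is the system-wide change among all homeless adults using any front door.
- From the trajectory variable already planned, report the monthly share of index episodes with an SCRT contact beside each ITS estimate.
- Add a sensitivity ITS that leaves out SCRT-entry episodes, to show how far a change in case mix may drive the result. It removes treated people as well as newly captured ones, so it is a check and not an effect estimate.

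In the Mixed methods analysis section, read a non-significant result from its confidence interval together with the SCRT share. Call it inconclusive about SCRT clients when the interval still includes a change that would matter at that share. Word the Discussion's aim to match.

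Do not report the estimate divided by the share as a per-contact effect. If it is given at all, mark it exploratory and state the assumptions of stable case mix and no spillover.

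The cost is one derived variable from data already linked, one extra model per outcome, and more cautious conclusions.

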#### Covariates

Demographic variables for age at time of service, gender identity, sexual orientation, race/ethnicity, housing status and insurance status will be developed in accordance with existing SFDPH reporting guidelines. Gender identity will be determined by information on each person’s sex at birth as well as self-reported gender identity to create categories for cisgender male or female, transgender male or female, and genderqueer or nonbinary. Sexual orientation is based on self-report. Race and ethnicity are recorded separately in both EHR systems and will be cross-referenced and then combined into a single variable by replacing race with ethnicity for those who identify as Hispanic/Latinx [22]. SFDPH defines someone as a person experiencing homelessness if they utilize a service that indicates housing instability (e.g., emergency shelter) or self-report homelessness while accessing health care services. Insurance status at the time of an encounter will be based on EHR billing records and grouped into descriptive categories (e.g., private versus public insurance). A location variable using zip code will be based on last location documented prior to the crisis episode. Multiple imputation will be used to account for missing data.

Diagnoses associated with service encounters will be categorized using the primary ICD-10 diagnostic code based on the Health Care Utilization Project’s Clinical Classifications Software Refined (CCSR) [23]. Given the unreliability of diagnosis data at the time of a crisis encounter [24, 25], we will use diagnoses made in routine service settings in the 90 days prior to the index crisis episode and, only if routine care is unavailable, will use acute-care settings diagnoses.

Additional clinical variables will include whether the index crisis episode resulted in an involuntary psychiatric hold; suicidality as part of the presentation (based on ICD-10 Z codes as well as clinical documentation or indication for involuntary holds as “danger to self”); and violence risk (based on clinical documentation or indication for involuntary holds as “danger to others”) [26]. We will also control for continuous variables describing the number of crisis services, routine care, jail, or housing assessment encounters in the 12-months prior to the index crisis episode. We will also assess the number of crisis services, routine care, jail, or housing assessment encounters in the 12-months prior to the index crisis episode.

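### In the pilot versus non-pilot comparison, exposure is set by zip code and period but the only correlation named is within person; if outcomes drift differently across zip codes, its standard errors will be too small

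*Protocol article*

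**What the plan says.** All places are in the Protocol article.

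- **Variance method** (Interrupted time series analysis): "Generalized estimating equations (GEE) will be used, with robust standard errors to account for within-person correlation". The sentence describes the trends across the three implementation periods.
- **Between-site comparison** (same section): the first safeguard for internal validity uses two nonequivalent groups, defined as "crisis episodes with zip codes corresponding to neighborhoods that did or did not have the SCRT active during the partial implementation phase". This design "will allow for a between-site comparison of the pilot catchment area relative to the non-pilot areas".
- **Other correlation** (same section): "Additional issues such as autocorrelation of repeated measures on individuals will be corrected for in the final analyses".
- **Roll-out** (Program): "The SCRT was first piloted in San Francisco’s highest demand neighborhoods in December 2020 and then was incrementally expanded to be citywide by June 2021".
- **Zip code elsewhere** (Covariates): "A location variable using zip code will be based on last location documented prior to the crisis episode". It may also enter the mean model, since "Models will be adjusted by the covariates described above and interaction terms constructed".

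No section mentions correlation within areas, area-by-time variation or a correction for few clusters.

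**The concern.** In the between-site comparison, everyone in a zip code changes exposure together. The quantity of interest is the change in pilot areas minus the change in non-pilot areas. A shock that hits the whole city in one month cancels in that difference. A change confined to some zip codes, such as a shelter opening or a shift in local outreach, does not.

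A standard error clustered on person treats people in the same zip code as independent. It therefore has no term for zip-specific change, and more episodes cannot make up for that. At stake is the first-listed defence against threats to internal validity. If areas merely drifted apart, a nominally significant pilot effect could be read as confirming the main time series result.

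**Working it through.** **Inputs from the article.** Baseline November 2019 to November 2020 is 13 months. Partial implementation December 2020 to July 2021 is 8 months. The article states no zip code count, episode count, outcome rate or intraclass correlation, so there is no figure of its own to reproduce. Everything below that is not a date is an assumption.

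**Step 1: what is left out.** Let D be the pilot change minus the non-pilot change, with g1 pilot and g0 non-pilot zip codes of equal size, and a zip-by-period effect with standard deviation τ. Then

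Var(D) = V + 2τ²(1/g1 + 1/g0),

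where V is the sampling variance. Person clustering estimates V only (the further within-person term is ignored in this hand calculation). The second term does not shrink as episodes accumulate.

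**Step 2: numbers.** Assume 12 zip codes, 4 of them pilot, 600 index episodes a month and an outcome rate of 35%, so p(1−p) = 0.2275. With a third of episodes in pilot areas, the cells hold 2,600 and 1,600 (pilot, before and during) and 5,200 and 3,200 (non-pilot).

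- V = 0.2275 × (1/2600 + 1/1600 + 1/5200 + 1/3200) = 0.000345.
- τ = 2 points (zip-by-period intraclass correlation 0.0004/0.2275 = 0.002): omitted term = 2 × 0.0004 × (1/4 + 1/8) = 0.00030. Variance ratio = (0.000345 + 0.00030)/0.000345 = 1.87. Actual type I error = 2 × (1 − Φ(1.96/√1.87)) = 15%.
- τ = 4 points (0.0016/0.2275 = 0.007): omitted term = 0.00120, ratio 4.48, actual type I error 35%.

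**Step 3: simulation with repeated episodes per person and unequal zip codes.** No SCRT effect, linear probability model, 400 runs per setting (Monte Carlo standard error about 1 point near 5% and 2 points near 25%). Rejection rates at nominal 5%, without zip fixed effects:

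| Zip codes (pilot) | Episodes per month | τ | Person-clustered | Zip-clustered, uncorrected, t reference |
|---|---|---|---|---|
| 12 (4) | 300 | 0 | 5.0% | 8.5% |
| 12 (4) | 300 | 2 points | 10.0% | 10.0% |
| 12 (4) | 300 | 4 points | 24.3% | 10.0% |
| 12 (4) | 600 | 0 | 4.0% | 9.8% |
| 12 (4) | 600 | 2 points | 19.8% | 11.0% |
| 12 (4) | 600 | 4 points | 37.8% | 10.0% |
| 25 (6) | 300 | 0 | 7.0% | 11.5% |
| 25 (6) | 300 | 2 points | 9.8% | 10.8% |
| 25 (6) | 300 | 4 points | 16.3% | 12.0% |
| 25 (6) | 600 | 0 | 3.0% | 8.5% |
| 25 (6) | 600 | 2 points | 10.5% | 8.0% |
| 25 (6) | 600 | 4 points | 26.8% | 8.5% |

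Adding zip code to the mean model does not help: 26.5% with it against 24.3% without (12 zip codes, 300 a month, τ = 4 points). It removes constant differences between zip codes, not different changes over time.

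**Step 4: a second set of assumptions.** 20 zip codes, 4 of them pilot, outcome rate 30%, three person-months per person with within-person correlation 0.3, 1,000 runs. The zip-by-period intraclass correlation is the total zip correlation times its zip-by-period share.

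| People per month | Zip-by-period correlation | Person-clustered rejection |
|---|---|---|
| Base case | 0 | 5.6% |
| 300 | 0.01 × 10% = 0.001 | 6% |
| 600 | 0.01 × 20% = 0.002 | 9% |
| 600 | 0.05 × 10% = 0.005 | 14% |
| 300 | 0.05 × 20% = 0.010 | 16% |
| 600 | 0.05 × 20% = 0.010 | 23% |
| 1,200 | 0.05 × 20% = 0.010 | 37% |
| 600 | 0.05 × 50% = 0.025 | 40% |

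A zip-level t test or a permutation test stayed at about 4-6% throughout. The permutation result relies on zip codes being exchangeable, which the simulation builds in.

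**Simplifications.** Both simulations hold pilot status fixed for all 8 partial months. The first also keeps each person in one zip code.

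**The case against.** The strongest reply is that the variance sentence belongs to the overall time series and that no model is given for the between-site comparison. The list of further corrections is also open-ended, and a condensed article may leave the clustering of one supporting comparison to a fuller plan. This stands in part: an area-level correction is not ruled out. But the section introduces the comparison as a strategy of this same analysis and names a clustering unit. That unit does not fit an area contrast, and the one further correction it names concerns individuals again. A plan that follows the text carries the mismatch forward.

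A second reply is that the mechanism needs zip-by-period variation, which the article does not quantify, and that nothing in the text says how many zip codes were in the pilot. This stands in full and makes the point conditional.

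Third, the comparison is one of three supporting strategies. No decision rule depends on it, and Limitations allows that incomplete location data may prevent it. This limits the consequence but does not remove the mismatch if the comparison is run.

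A reader might go further and infer that the test is too liberal whatever the data, or that a single rejection rate such as 23% describes this study. The documents support neither. With no zip-by-period variation the person-clustered test is close to nominal (3-7% in one simulation, 5.6% in the other), and 23% is one assumed setting among many. Nor does the point extend to the citywide time series or the within-site sub-analyses, which contrast no areas.

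**Conclusion.** The point holds conditionally, for the between-site contrast alone. Exposure there varies by zip code and period, while the only correlation the article names is within person. If outcomes drift differently across zip codes between periods, the stated standard errors are too small. Such drift is plausible because pilot areas were selected for demand rather than at random, but it is unmeasured here.

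Under the assumptions shown, actual type I error at nominal 5% is about 5-6% with negligible zip-by-period variation and roughly 10-40% with modest to large variation. It grows with the number of episodes per month. These figures illustrate a range and are not estimates for this study. The plan should be amended before the comparison is run; the main analysis does not depend on it.

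**What to change.** For the pilot versus non-pilot contrast only:

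1. Base intervals and p-values on the zip code or roll-out area as the cluster, with a few-cluster method: a bias-corrected area-clustered standard error with a t reference, a wild cluster bootstrap, or a zip-level analysis of change. An uncorrected sandwich by zip code is not enough, since it rejected 8-13% of the time in the first simulation, with or without zip fixed effects.
2. Allow for people who appear in more than one zip code. Location is the last one documented before each episode, so people need not be nested in areas.
3. Code exposure by each area's actual launch date. Expansion was citywide by June 2021, so July 2021 at least falls in the partial period with no untreated area left.
4. Use permutation of pilot status only as a sensitivity check. Pilot areas were the highest-demand neighborhoods and are not clearly exchangeable with the rest.
5. Keep person clustering for the citywide time series and the within-site sub-analyses.

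The cost is a few sentences in the plan and some code; zip codes are already in the limited dataset. The price is wider intervals and possibly low power if few zip codes were in the pilot. In that case, report the comparison as descriptive support only.
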